#### Participants’ safety and adverse effects monitoring management

2.8.1

Even though the proposed project is not expected to pose any risks for participants, the proposed research protocol incorporates measures to ensure participant safety and minimize risks associated with the nutritional intervention and other study procedures. Trimestrial administration of standard 2-h OGTT is considered safe for both the expecting mothers and their fetuses, as this test is performed as part of usual prenatal care. Data monitoring will be constantly done by the treating physicians and the results of all OGTTs will be validated by an endocrinologist. Hence, participation in this project can allow early identification and prompt management of GDM in some participants. The nutritional intervention provided aims to improve diet quality and glycemic profile. Thus, it is very unlikely to cause any safety issues as it is already recommended during pregnancy in individuals with GDM. Moreover, since this intervention does not involve any caloric restriction or strict recommendations, it is not expected to pose any risks such as insufficient weight gain or ketonuria for the participants.

Since the study is open-label, even if very unlikely, it will be easy to determine whether clinical problems that occur are related to the intervention. However, to ensure safety monitoring, adverse events will be closely monitored. Adverse events will be classified into two categories:

Adverse Events of Special Interest refer to any undesirable occurrence experienced by a study participant during the trial, whether or not considered related to the provided intervention, and include the following:

⚬ vomiting during the oral glucose tolerance test;⚬ loss of consciousness during the oral glucose tolerance test;⚬ thromboembolic event during pregnancy;GDM;⚬ gestational hypertensive disorder (gestational hypertension, preeclampsia, and eclampsia);⚬ preterm birth (occurring after 22 weeks and before 37 weeks of gestational age); and⚬ spontaneous abortion or miscarriage (i.e., < 22 weeks of gestational age).

Serious Adverse Events are defined as any untoward medical occurrence that results in inpatient hospitalization or prolongation of existing hospitalization, severe congenital malformation or death, whether or not considered related to the provided intervention, and include the following:

⚬ hospitalization (other than for childbirth);⚬ late fetal loss (i.e., fetal death between 22 and 28 weeks of gestational age);⚬ stillbirth (i.e., > 28 weeks of gestational age);⚬ neonatal death (between birth and before 28 days of life);⚬ newborn with severe congenital malformation (causing functional disability); and⚬ admission of the newborn to the intensive care unit.

During their participation, all study participants will be closely monitored for the occurrence of adverse events. Upon identification of an adverse event, the investigator will assess its severity (mild, moderate, or severe), its expectancy, and its causality. If needed, the investigator will take appropriate actions. The trial steering and monitoring committees will also be notified with relevant information on adverse events for their review.

### Bias and retention strategies

2.9

Due to the nature of the study, blinding of the research team and participants will not be possible. However, the online computerized allocation used will prevent allocation bias. Ascertainment bias cannot be prevented as this RCT involves a treatment in which active participation is necessary and participants cannot be blinded to the intervention or the GDM diagnosis. Withdrawal bias will be assessed by appropriate data analyses. Efforts will be made to eliminate publication bias through the registration of our trial at inception (NCT05299502) and publication of the results in peer-reviewed journals. Finally, outcomes are objective and standardized, and hence difficult to bias.

The expected rate of withdrawal and loss to follow-up is approximated at 10% based on similar trials during pregnancy (24, 26, 89). A greater loss to follow-up is expected in the control group, as observed in other RCTs (24, 26, 89). Conservatively, we calculated a sample reduction of 20%.

To maximize retention, for both groups, we will ensure a close and personalized follow-up for each participant and all questions and concerns will be answered promptly. A financial compensation of $20 is also offered to participants to thank them for attending each research visit. For the control group, they are offered a free 1-h consultation with an RD from our team, upon completion of the study. For the intervention group, the fact that the RD is always available via the Facebook community will be an advantage for the retention of our participants. The option to meet with the RD virtually also represents a benefit. As previously mentioned, nutritional intervention compliance, as well as attendance at each consultation will be recorded. Video clip views and engagement to the Facebook group will also be tabulated (likes, comments, and views). Based on RCTs during pregnancy (90) and our previous studies, we conservatively expect a compliance rate of 85%.

### Sample size calculation and statistical analysis

2.10

#### Sample size calculation

2.10.1

The sample size calculation for our study is predicated on relevant prior research (5, 91). First, data from one of our previous studies conducted among a sample including pregnant people at risk for GDM indicates that the mean change in FPG from the first to the third trimester was an increase of 0.4 ± 0.8 mmol/L, which is what we expect to find in the control group (91). Second, it was previously demonstrated that an increase of 0.4 mmol/L (1 SD) in FPG in the third trimester is significantly associated with higher odds of unfavorable perinatal outcomes. Our sample size calculation was therefore primarily centered on these findings, as it aims to enable the detection of a minimal clinically significant difference between groups, specifically a 0.4 mmol/L change in delta FPG levels from the first to the third trimester. We postulate that the control group will experience an FPG increase of 0.4 ± 0.8 mmol/L, per previous observations, while the intervention group is anticipated to maintain stable FPG levels (0.0 ± 0.8 mmol/L) (effect size of 0.5). To ensure a statistical power of 80% in detecting this clinically significant 0.4 mmol/L difference between groups, with a significance level (alpha) set at 0.05, we have factored in two considerations. First, we assume a 4% pregnancy loss (92), and an 8% premature delivery (93). Second, given the nature of the study and drawing from experiences and other relevant research, we conservatively anticipate a dropout rate of 20% (24, 26, 89). Consequently, we are in the process of recruiting a total of 150 pregnant women for our study.

#### Statistical analyses

2.10.2

The primary analyses will follow the complete case intention-to-treat principle. Changes from first- to third-trimester measurements of the primary and secondary outcomes between the intervention and control groups will be assessed using a two-sample one-sided *t*-test for means. To determine whether the results obtained depend on an improvement in diet quality, a generalized linear model will be used. Sensitivity analyses will be performed on all outcomes to (1) determine if missingness of the outcome data is associated with prognostic characteristics at baseline and treatment group; (2) compare the results obtained with those following an intention-to-treat analysis where missing outcomes are handled using multiple imputation by chained equations, an analysis on a complete case per protocol, and a per-protocol analysis where missing outcomes are handled using multiple imputation by chained equations; and (3) to explore potential sources of heterogeneity in treatment effects. We thus plan to test the effect of various covariables including age, pre-pregnancy BMI, parity, gestational weight gain, GDM risk factors, fasting blood glucose in the first trimester, GDM diagnosis in the second trimester, adherence to the intervention (with a weighted model based on the level of participation in the intervention), and intervention delivery mode (in person of virtually). Those analyses will ensure a more comprehensive understanding of how different factors may influence the intervention’s outcomes in diverse subgroups of the study population. Programming codes will be tested with a dummy data set to ensure their validity. No preliminary or interim analyses are planned. An exploratory health-economic analysis could be conducted *post hoc*.

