### Randomization

2.6

Randomization occurs after the eligibility assessment and completion of the V1 and associated questionnaires mentioned below. Group allocation is concealed using online computerized randomization by FANI (*Application Fonctionnelle de Nutrition sur Internet*), a Web platform developed and hosted by the Institut sur la nutrition et les aliments fonctionnels, Université Laval. Eligible subjects will be randomized to the intervention or control group at a ratio of 1:1. The randomization order is generated independently using online computerized group allocation with a permuted block of variable block sizes (4–10). The participant’s treatment allocation is then automatically and electronically delivered to the local site investigator and research staff. Randomization is performed over the phone with the candidate after confirmation of her willingness to participate. Group allocation is then provided immediately to the participant.

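### The primary analysis leaves out first-trimester FPG, which is measured before randomisation; adding it to the model costs one degree of freedom and can only hold or raise precision

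*Protocol article*

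**What the plan says.** The primary outcome is the change in FPG from the first to the third trimester (Study objective and outcomes). The Statistical analyses section fixes the test. The quantities compared are "Changes from first- to third-trimester measurements of the primary and secondary outcomes between the intervention and control groups", on a complete-case intention-to-treat basis, and the method is a one-sided t-test for two independent samples. No covariate is named for this comparison.

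First-trimester fasting glucose appears once in that section, in a list of covariables whose effects will be tested as part of the sensitivity analyses exploring heterogeneity of the treatment effect. The same list holds gestational weight gain, second-trimester GDM diagnosis, adherence and delivery mode, all of which arise after randomisation.

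Fasting glucose is drawn at every visit (Glucose homeostasis outcomes), and participants are randomised only after Visit 1 is complete (Randomization). Allocation uses a "permuted block of variable block sizes (4–10"), and the article states no stratification factor.

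The sample size targets "specifically a 0.4 mmol/L change in delta FPG levels from the first to the third trimester", assumes that "the control group will experience an FPG increase of 0.4 ± 0.8 mmol/L" with the same SD in the intervention arm, and works "with a significance level (alpha) set at 0.05".

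**The concern.** A t-test on change is a regression in which the coefficient of third-trimester on first-trimester FPG is set to 1 rather than estimated. If the true slope differs from 1, part of the variation that baseline FPG could explain stays in the error term, and the estimate moves with any chance baseline difference between arms.

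The covariate is already in hand. Visit 1 FPG is needed to confirm eligibility, so every randomised participant should have a value. The planned power is only just above 80%, so spare precision is worth having. The heterogeneity analyses do not supply the missing estimate. They are exploratory, and with variables measured after randomisation among the covariables they do not define a baseline-adjusted treatment effect.

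**Working it through.** **Inputs from the protocol article.** Difference in change 0.4 mmol/L; SD of change 0.8 mmol/L in each arm (standardised effect 0.5); alpha 0.05; power 80%; one-sided t-test; 1:1 allocation; losses of 4% (pregnancy loss), 8% (premature delivery) and 20% (dropout); 150 recruited.

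**Inputs not in the article (assumed).** The correlation r between first- and third-trimester FPG, taken as 0.3, 0.5 and 0.7, and the SDs at the two visits.

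**1. Reproduce the stated 150.** A one-sided t-test at 0.05 with standardised effect 0.5 needs 51 per arm for 80% power, or 102 evaluable. Adding the losses gives 4% + 8% + 20% = 32%, and 102/0.68 = 150. The sample size therefore rests on the unadjusted change-score SD of 0.8. Power at 51 per arm is 81%.

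**2. ANCOVA with equal SDs at both visits.** With common visit SD s, the change-score variance is 2s²(1 − r) and the ANCOVA residual variance is s²(1 − r²). The ratio is (1 + r)/2, so the residual SD is 0.8 × √((1 + r)/2).

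| r | Variance ratio | Residual SD | One-sided power, 51 per arm |
|---|---|---|---|
| Unadjusted change | 1 | 0.800 | 81% |
| 0.3 | 0.65 | 0.645 | 93% |
| 0.5 | 0.75 | 0.693 | 89% |
| 0.7 | 0.85 | 0.738 | 86% |

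A simulation of 20,000 trials per setting gave 80–81% for the t-test on change and 92%, 89% and 86% for ANCOVA. Type I error was about 5% for both.

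**3. ANCOVA with unequal SDs.** Hold the change SD at 0.8 and assume a Visit 1 SD of 0.4. The Visit 3 SD, s₃, then solves s₃² + 0.16 − 0.8·r·s₃ = 0.64. The slope is r·s₃/0.4 and the residual variance is s₃²(1 − r²), compared with 0.8² = 0.64.

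| r | s₃ | Slope | Residual SD | Variance reduction | One-sided power, 51 per arm |
|---|---|---|---|---|---|
| 0.3 | 0.82 | 0.62 | 0.785 | 4% | 82% |
| 0.5 | 0.92 | 1.15 | 0.798 | 1% | 81% |
| 0.7 | 1.03 | 1.80 | 0.734 | 16% | 86% |

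The gain shrinks towards zero as the slope approaches 1 and returns on either side of it.

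**4. Chance imbalance.** A Visit 1 difference of 0.1 mmol/L shifts the change-score estimate by (1 − slope) × 0.1 in the opposite direction. In the equal-SD case the slope equals r, so the shift is 0.07, 0.05 or 0.03 mmol/L. The standard error of the unadjusted difference is 0.8 × √(2/51) = 0.158, so a shift of 0.05 is about 0.3 standard errors.

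**The case against.** The strongest reply is that nothing here is wrong. The outcome is defined as a change, the test compares that change, the sample size matches the test, and the planned one-sided power is already 81%. That stands. The t-test is unbiased over randomisation and holds its type I error, so this is a point about efficiency.

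The size of the gain is also undetermined. The equal-SD case implies visit SDs of 0.68, 0.80 and 1.03 at r = 0.3, 0.5 and 0.7, none of which the article gives. Its only visit-level SD is 0.4, quoted for the third trimester. Assigned to Visit 3, that figure would make the residual variance at most 0.16 against 0.64, a larger gain. The scenario in step 3 assigns 0.4 to Visit 1 by assumption and shows how small the gain can be. The direction is secure; the magnitude is not.

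Three stronger readings are tempting and are not supported:

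- A reader might infer that chance imbalance biases the planned test. It does not. The shift in step 4 is sampling error already inside the t-test's standard error, and removing it is the same benefit as the precision gain, not a second one. Nor does the change score always over-correct: with a slope above 1 it under-corrects.
- A reader might infer that adjustment would pay for a move to a two-sided test. That holds only in some scenarios. Two-sided power at 51 per arm is 71% unadjusted and about 87%, 82% and 77% adjusted with equal SDs, but it stays at 72% and 71% for r = 0.3 and 0.5 when the Visit 1 SD is 0.4. Sidedness is a separate matter.
- A reader might infer that randomisation is known to be unstratified. The article, which condenses the full protocol, states no strata; it does not say that there are none.

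**Conclusion.** The point holds as an improvement that costs nothing in data, not as an error. The article fixes the primary test without a covariate, so this is not a detail left to an unseen analysis plan. Adjusting for first-trimester FPG is at least as efficient as the planned test, apart from one degree of freedom in about 100.

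Under the planned one-sided 0.05 test with 51 per arm, power lies between 81% (no gain) and about 93% across the scenarios examined. That range depends on assumed correlations of 0.3 to 0.7 and assumed visit SDs. No change to the validity of the trial or to its sample size follows.

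**What to change.** Before any outcome data are analysed, prespecify the primary analysis as a linear model of third-trimester FPG on arm and first-trimester FPG. Modelling the change with the same covariate gives the same treatment estimate. Name the covariate set in full and fix it in advance: the trial is open-label, and an optional extra covariate would leave the primary model open to choice. Keep gestational weight gain, second-trimester GDM, adherence and every other post-randomisation variable out of it.

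Analyse each secondary index in the same way with its own Visit 1 value. Keep the unadjusted t-test on change as a sensitivity analysis.

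The cost is a few sentences in the analysis plan, one model statement and one degree of freedom. The target of 150 and the data collection schedule stay as they are.

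### The 80% power with 150 participants rests on a one-sided 5% test, so a false claim of benefit has a 5% chance rather than 2.5%; the sample size section does not state this

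*Protocol article*

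**What the plan says.** All references are to the protocol article.

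- **Test (2.10.2).** For the primary endpoint and the secondary ones alike, differences in change "between the intervention and control groups will be assessed using a two-sample one-sided" version of the t-test, on complete cases by randomised group. No reason is given for a one-sided test.
- **Power (2.10.1).** The aim is given as "To ensure a statistical power of 80% in detecting this clinically significant 0.4 mmol/L difference between groups". The error rate follows: the calculation was made "with a significance level (alpha) set at 0.05". This section does not say whether alpha is one- or two-sided.
- **Effect (2.10.1).** The assumption for usual care reads "We postulate that the control group will experience an FPG increase of 0.4 ± 0.8 mmol/L". For the other arm, the article says that "the intervention group is anticipated to maintain stable FPG levels (0.0 ± 0.8 mmol/L) (effect size of 0.5"). The difference to be detected is described as "specifically a 0.4 mmol/L change in delta FPG levels from the first to the third trimester".
- **Losses (2.10.1).** 4% pregnancy loss, 8% premature delivery and 20% dropout, leading to 150 recruited. Section 2.9 expects about 10% withdrawal and loss to follow-up, then adds: "Conservatively, we calculated a sample reduction of 20" per cent.
- **Allocation (2.6).** "Eligible subjects will be randomized to the intervention or control group at a ratio of 1:1".
- **Hypothesis (1.4).** Directional: the intervention is expected to improve the glucose measures.

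**The concern.** A power claim at alpha 0.05 with no sidedness can easily be read as two-sided. Here the planned test is one-sided, and alpha has not been lowered to 0.025 to compensate. A favourable result with a two-sided p-value of up to 0.10 would count as positive. The discussion says that favourable results would lead to steps to integrate the intervention into care and could inform guidelines and policy, so the evidential standard for the primary conclusion matters.

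A one-sided test towards benefit also gives no route to a significant finding in the other direction. If FPG rose more in the intervention arm, the formal result could only be non-significant.

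**Working it through.** **Inputs.** Difference 0.4 mmol/L, SD 0.8, so d = 0.4/0.8 = 0.5; alpha 0.05; power 80%; losses 4%, 8% and 20% (all 2.10.1); 1:1 allocation (2.6); complete-case analysis, so losses reduce the analysed sample (2.10.2).

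**Step 1: reproduce 150.** Power of the two-sample t-test comes from the noncentral t distribution with noncentrality d × √(n/2) and 2n − 2 degrees of freedom, where n is the number per arm.

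- One-sided 5%: 50 per arm gives 79.9% and 51 per arm gives 80.6%. So 51 per arm, or 102 evaluable.
- Losses added: 4% + 8% + 20% = 32%. Then 102/(1 − 0.32) = 102/0.68 = 150.0, the planned total.
- Losses multiplied: 102/(0.96 × 0.92 × 0.80) = 144.4, or 146 in equal arms. This is close but not exact.

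**Step 2: the same inputs at two-sided 5%.** The requirement is 64 per arm (80.2% power), or 128 evaluable.

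- 20% loss only: 128/0.80 = 160 enrolled.
- Losses multiplied: 128/(0.96 × 0.92 × 0.80) = 181.2, so 182.
- Losses added: 128/0.68 = 188.2, so 190 in equal arms.

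None of these gives 150.

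**Step 3: power with 150 enrolled.**

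| Loss assumed | Evaluable | Per arm | One-sided 5% | Two-sided 5% |
|---|---|---|---|---|
| 32% (4% + 8% + 20%) | 102 | 51 | 80.6% | 70.6% |
| Multiplied | 106 | 53 | 81.9% | 72.2% |
| 20% dropout only | 120 | 60 | 85.9% | 77.5% |
| 10% (expected rate, 2.9) | 135 | 67.5 | 89.3% | 82.2% |

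**Step 4: what the choice of tail changes.** With 51 per arm, the standard error of the difference is 0.8 × √(2/51) = 0.158. The critical t value on 100 degrees of freedom is 1.660 one-sided and 1.984 two-sided. The smallest observed benefit declared significant is therefore 1.660 × 0.158 = 0.26 mmol/L under the plan, against 1.984 × 0.158 = 0.31 mmol/L under a two-sided 5% test. With no true effect, the chance of crossing the threshold towards benefit is 5% and 2.5% respectively.

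**Step 5: what baseline adjustment could recover.** Assume equal variances at the two visits and correlation r between them. The variance of the change is 2σ²(1 − r) and the residual variance after adjustment is σ²(1 − r²). Their ratio is (1 + r)/2, so the effective d is 0.5 × √(2/(1 + r)). Two-sided 5% power with 51 per arm (99 degrees of freedom):

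| r | Effective d | Power |
|---|---|---|
| 0.4 | 0.598 | 85% |
| 0.5 | 0.577 | 82% |
| 0.6 | 0.559 | 80% |
| 0.7 | 0.542 | 77% |

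The article does not give r, so this range is an assumption.

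**The case against.** The best defence is that the plan is coherent. The hypothesis is directional, the one-sided test is prespecified, its sidedness appears in the subsection directly after the power claim, and 150 follows exactly from it. All of that stands. A reader might infer that the 80% is wrong or that the two subsections contradict each other; under the plan's own test, neither is so.

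Four other stronger readings also fail or need limits.

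- **That the trial has 80% power only if the test is one-sided.** This depends on the losses. At the 10% loss that 2.9 expects, two-sided power is about 82%. The 71% figure also assumes that every premature delivery loses the third visit. That visit is at 34–36 weeks, and 2.8.1 defines preterm birth as before 37 weeks, so some of those participants could attend. If none of the 8% were lost, 150 × 0.76 = 114 would be evaluable and two-sided power about 75%. A range is more accurate than a single figure.
- **That 2.9 and 2.10.1 disagree on attrition.** They do not. Section 2.9 concerns withdrawal and loss to follow-up, and 2.10.1 uses the same 20% for dropout. The 4% and 8% are listed as separate losses.
- **That one-sided testing breaks down because some secondary outcomes improve by falling and others by rising.** The tail can differ by outcome, and 1.4 sets the direction as improvement. Opposite directions are not in themselves a defect.
- **That false-positive risk doubles, or that harm cannot be seen.** Total nominal type I error remains 5%; only the chance of a false claim of benefit doubles. The test cannot declare harm if its tail follows the hypothesis in 1.4, but estimates and intervals can still be reported, and GDM is recorded both as an outcome and as an adverse event of special interest.

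These points narrow the concern. They do not supply a reason for a one-sided 5% test in a trial meant to inform care.

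**Conclusion.** The concern holds as a choice of evidential standard that is not stated beside the power claim. It is not an arithmetic error. Under the planned test, 150 gives 80.6% power after all stated losses, at the price of a 5% chance of falsely declaring benefit instead of 2.5%, and with no possibility of declaring a worse FPG significant. Judged at two-sided 5%, unadjusted power is about 71% (all stated losses, 102 evaluable) to 78% (20% dropout only, 120 evaluable).

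These figures rest on the article's difference of 0.4, SD of 0.8 and equal arms. The statement about harm assumes that the tail follows the improvement hypothesis, because 2.10.2 does not name the direction.

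**What to change.** 1. **Section 2.10.2.** Test the primary and secondary outcomes two-sided at 5% (for a claim of benefit, equivalent to one-sided 2.5%) and report 95% confidence intervals.
2. **Section 2.10.2.** Make the primary analysis a comparison of third-trimester FPG between arms adjusted for first-trimester FPG. First-trimester FPG is already collected and already listed among the covariables.
3. **Section 2.10.1.** State that 150 was sized on a one-sided 5% test with losses of 4%, 8% and 20%. Give the unadjusted two-sided power as about 71% (102 evaluable) to 78% (120 evaluable).

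**Cost.** The change is one of wording and needs no extra participants. The stated unadjusted power falls below 80%. Under equal variances, adjustment brings 51 per arm back to about 80% or more if the correlation is about 0.6 or lower, and to 77% at 0.7; the gain should not be promised, because the article gives no correlation. No interim analysis is planned, so the change can be made before any comparison of outcomes by arm. If the sponsor keeps the one-sided 5% test, the minimum is to justify it and state the sidedness next to the power claim.

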Our choice to prioritize nutrition intervention, rather than covering areas such as physical activity or other lifestyle habits, is primarily based on the simplification of the intervention that takes into account the reality that pregnant individuals are often faced with a multitude of responsibilities and concerns, which can lead them to feel overwhelmed, especially as their time to meet with several health professionals is limited (63). This simpler approach aims to enhance adherence to the program and facilitate the achievement of individual goals and have the potential to be implemented with perinatal care. This choice is also based on the fact that diet-based interventions have been associated with a reduced risk of GDM while mixed-approach interventions seem to be less effective (64). Moreover, current literature clearly demonstrates that pregnant individuals are motivated to eat well during pregnancy and require help to do so (65, 66). Finally, by choosing to target nutrition, we also avoid having to interrupt the intervention due to physical activity contraindications (67, 68). However, we do not deny the importance of staying active during pregnancy, which is suggested by recent Canadian recommendations (67). Physical activity will be measured every trimester to control for this confounding factor. Participants having questions about physical activity will be referred to their general practitioner or a kinesiologist.

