#### Both groups

2.6.3

Participants with a positive diabetes diagnosis in the first trimester are excluded. However, if a GDM is diagnosed during the second or third research visits, participants remain in the project. In the second and third trimesters (V2 and V3), GDM will be diagnosed using the alternate one-step approach suggested by Diabetes Canada’s latest guidelines and the International Association of the Diabetes and Pregnancy Study Groups based on the Hyperglycemia and Adverse Pregnancy Outcome study (5). Therefore, GDM will be diagnosed if one plasma glucose value is abnormal (FPG ≥ 5.1 mmol/L, 1 h following the ingestion of 75 g of glucose ≥10.0 mmol/L, 2 h following the ingestion of 75 g of glucose ≥8.5 mmol/L) (2). The usual conduct for GDM management is to refer to the multidisciplinary team for pregnancies at risk in hospitals or clinics and nutritional therapy is usually initiated within a few weeks (2). Hence, participants diagnosed with GDM will be referred and followed by a multidisciplinary team including RDs, regardless of their group allocation. Since the diagnosis of GDM in the second trimester and the resulting treatment received by the participants may interfere with our results, the effect of this added care will be monitored through retrospective patient medical record data collection and considered in our statistical analyses. However, a late diagnosis at V3 and its subsequent management are not expected to interfere with the results collected at V3 and will therefore not be considered in analyzing our primary and secondary outcomes. Participants are also instructed to contact the research staff between visits or phone calls if they are diagnosed with GDM outside of research visits or if any relevant situations occur during their participation, making them no longer eligible for the study or unable to complete their participation.

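### The exploratory heterogeneity analyses list four post-randomisation variables (weight gain, second-trimester GDM, adherence, delivery mode) beside baseline factors, and the handling of GDM care does not fit the planned t-test

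*Protocol article*

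**What the plan says.** All references are to the protocol article.

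- **Main analysis (2.10.2).** "The primary analyses will follow the complete case intention-to-treat principle". First- to third-trimester changes in the primary and secondary outcomes "will be assessed using a two-sample one-sided *t*-test for means". No covariate is named for this test.
- **Covariate list (2.10.2).** The third sensitivity analysis is meant "to explore potential sources of heterogeneity in treatment effects". The text continues: "We thus plan to test the effect of various covariables including age, pre-pregnancy BMI, parity, gestational weight gain, GDM risk factors". Items from before and after randomisation stand side by side: "gestational weight gain, GDM risk factors, fasting blood glucose in the first trimester, GDM diagnosis in the second trimester, adherence to the intervention". Adherence enters through a weighted model "based on the level of participation in the intervention), and intervention delivery mode (in person of virtually"). The section does not say whether the terms are main effects, adjustment terms or interactions with arm.
- **GDM care (2.6.3).** Because treatment for GDM found in the second trimester may interfere with the results, "the effect of this added care will be monitored through retrospective patient medical record data collection and considered in our statistical analyses". A diagnosis at V3 is explicitly left out of the primary and secondary analyses.
- **Physical activity (2.6.1).** "Physical activity will be measured every trimester to control for this confounding factor".
- **Reliance on the adherence analysis (3, Discussion).** The limitations paragraph presents complete-case intention-to-treat, combined with adherence-weighted sensitivity analyses, as a way to limit the problems of non-compliance and dropout.

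**The concern.** Randomisation takes place after V1 (2.6). A variable fixed before that point can serve as an effect modifier or adjustment covariate without harm to the randomised comparison. A variable that arises later can be a consequence of the intervention. The list in 2.10.2 makes no distinction between the two kinds.

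At stake is how the supporting analyses will be read. The plan looks to them to explain the influence of GDM care, non-adherence and delivery mode in subgroups. Run as listed, they would give contrasts that are not randomised, or interaction terms that no data can identify, presented alongside valid baseline subgroup analyses.

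There is a further mismatch. Section 2.6.3 excludes only V3 diagnoses from the primary and secondary analyses, which suggests that second-trimester GDM care does bear on them. A plain two-sample t-test has no place for it.

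**Working it through.** **1. The plan's own sample size, to see what the list can affect.** Inputs from 2.10.1: difference 0.4 mmol/L, SD 0.8 (effect size 0.5), alpha 0.05, power 80%, losses of 4%, 8% and 20%. From 2.10.2: one-sided t-test. The exact noncentral-t calculation gives 51 per arm, 102 in total. Summed losses are 0.04 + 0.08 + 0.20 = 0.32, and 102 / (1 - 0.32) = 102 / 0.68 = 150. The stated N follows from the unadjusted test and does not depend on the covariate list.

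**2. Sorting the list by timing.**

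| Variable | Fixed before randomisation? | Source |
|---|---|---|
| Age, pre-pregnancy BMI, parity, GDM risk factors, first-trimester FPG | Yes | 2.3, 2.5, 2.6 |
| Gestational weight gain | No: last measured weight minus pre-pregnancy weight; also an exploratory outcome | 2.7.5.3, 1.5 |
| Second-trimester GDM | No: V2 is at 24–26 weeks, and FPG of 5.1 mmol/L or more is one criterion; also an exploratory outcome | 2.6.3, 1.5 |
| Adherence | No: intervention arm only | 2.6.1, 2.6.2 |
| Delivery mode | No: intervention arm only, chosen by the participant | 2.6.1, 2.6.2 |

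Second-trimester GDM is thus partly defined by an earlier measurement of the primary outcome variable.

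**3. Can the arm-by-mode interaction be estimated?** Take a model with intercept, arm (A), mode (M) and A×M. Controls have no mode, so M = 0 whenever A = 0, and A×M equals M in every row. The design matrix has 4 columns and rank 3, so the interaction is not identified. The same holds for adherence. A nested model with intercept, A and an in-person indicator set to 0 in controls has 3 columns and rank 3 and can be fitted. Its arm coefficient then compares virtual delivery with control, in groups the participants chose.

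**4. Adjusting for second-trimester GDM (illustration).** Assumptions not in the document: 20% GDM in controls, a 0.5 SD intervention effect on V2 glucose, and correlation ρ between V2 glucose and the FPG change. There were 2,000 simulated trials of 75 per arm, with a true difference of -0.40 and SD 0.8.

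| ρ | GDM-adjusted difference | Share of 0.40 lost |
|---|---|---|
| 0.3 | -0.354 | 1 - 0.354/0.40 = about 12% |
| 0.5 | -0.319 | 1 - 0.319/0.40 = about 20% |
| 0.7 | -0.285 | 1 - 0.285/0.40 = about 29% |

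**5. Adding an effect of GDM treatment on V3 FPG.** Assumptions: V1 SD 0.4, V2 SD 0.55, V2 effect -0.2, GDM in 29% of controls and 18% of the intervention arm, V1–V3 correlation 0.3–0.5, V2–V3 correlation 0.5–0.7.

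- If treatment lowers V3 FPG by 0.4, the unadjusted difference is about -(0.40 - 0.4 × (0.29 - 0.18)) = -0.356. The GDM-adjusted one is -0.32 to -0.36.
- If it lowers V3 FPG by 0.8, the unadjusted difference is about -(0.40 - 0.8 × 0.11) = -0.312. The adjusted one is still -0.32 to -0.36, now further from zero than the t-test.

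The direction of the shift is therefore not fixed.

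**6. Selecting adherers (illustration).** Suppose the analysis keeps only the adherent fraction p of the intervention arm against all controls, there is no true effect, and adherence correlates r with FPG change. The spurious difference is φ(q)/p × r × 0.8, where q is the normal quantile for p. At the 85% compliance expected in 2.9, φ(q)/p = 0.274, so r = 0.1 gives 0.274 × 0.1 × 0.8 = 0.02 mmol/L and r = 0.3 gives 0.07 mmol/L. The values of r are assumptions, and the article does not define its per-protocol set.

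**The case against.** The strongest reply is that the list is exploratory. The primary and secondary comparison is an unadjusted intention-to-treat t-test, the list is the third of the sensitivity analyses, and the text speaks of testing effects without using the word adjust. That stands. A reader might infer that the main treatment effect will be adjusted for post-randomisation variables and so be biased; 2.10.2 does not support this.

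Other stronger readings also fail:

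- **Adherence and delivery mode cannot be analysed at all.** Only their interaction with arm is inestimable. A within-arm contrast can be fitted, although it is self-selected.
- **Adjustment for GDM always biases towards no effect.** Step 5 of the working shows otherwise, and no calculation settles the direction for weight gain.
- **GDM diagnosed between V2 and V3 goes unrecorded.** Section 2.7.1 records GDM throughout the study, and 2.6.3 asks participants to report diagnoses made elsewhere. What is missing is a stated analytic handling, because the covariate covers second-trimester diagnoses only.
- **Participants with GDM are lost from the main analysis.** Section 2.6.3 keeps them in the project, and the V1-to-V2 change in FPG is already a secondary outcome.

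Physical activity is not in the 2.10.2 list, and it is also measured at V1. The objection in 2.6.1 is therefore limited to calling its later measurements a confounder of a randomised comparison.

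The reply does not rescue the list itself. Whether the four variables enter as adjustment terms or as interactions, the result is not a randomised effect or its modification, and the Discussion relies on one of these analyses.

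**Conclusion.** The point holds for the exploratory analyses. Four of the listed variables arise after randomisation. Conditioning on weight gain or second-trimester GDM no longer estimates the total randomised effect, and subgroups on them break the randomised comparison. Interactions of arm with adherence or delivery mode are not identified. These conclusions follow from the document's own timing and definitions and need no outside figure.

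The sizes do. A GDM-adjusted difference of -0.35 to -0.29 against a true -0.40 rests on assumed GDM rates, V2 effects and correlations, and on no effect of GDM treatment. It is an illustration, and a treatment effect can change both size and direction.

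The primary t-test and N = 150 are unaffected. Separately, 2.6.3 and 2.10.2 need reconciling: the promise to consider second-trimester GDM care has no counterpart in the planned main test.

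**What to change.** 1. Restrict effect-modifier and adjustment covariates to baseline variables: age, pre-pregnancy BMI, parity, GDM risk factors and V1 FPG. Do not treat physical activity measured after randomisation as a confounder.
2. Report adherence and delivery mode descriptively within the intervention arm. Label any adherence-weighted or per-protocol estimate as non-randomised, and amend the Discussion's reliance on it. A complier-average estimate may be added as a supplement if its exclusion restriction is stated. That restriction is doubtful for a session-attendance threshold, because calls, videos and the Facebook group may act on participants who attend few sessions.
3. Reconcile 2.6.3 with 2.10.2. State that the primary estimand uses V3 FPG regardless of GDM care. Handle any GDM treatment started before V3, including after a diagnosis between V2 and V3, in one labelled supplementary analysis. For example, set V3 FPG after such treatment to missing and multiply impute it from V1 and V2 values.

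Cost: changes of wording, minor extra programming, and extraction of the treatment start date from medical records that are already to be reviewed. Sample size, visits and care do not change.
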